### **8.3. Suspected unexpected serious adverse reactions (SUSAR)**

Adverse reactions are all untoward and unintended responses to an investigational product related to any dose administered.

Unexpected adverse reactions are adverse reaction, of which the nature, or severity, is not consistent with the applicable product information (Investigator's Brochure).

The sponsor will report expedited the following SUSARs to the METC:

- SUSARs that have arisen in the clinical trial that was assessed by the METC

- SUSARs that have arisen in other clinical trial of the same sponsor and with the same medicinal product, and that could have consequences for the safety of the subjects involved in the clinical trial that was assessed by the METC.

The remaining SUSARs are recorded in an overview list (line-listing) that will be submitted once every half year to the METC. This line-listing provides an overview of all SUSARs from the study medicine, accompanied by a brief report highlighting the main points of concern.

The sponsor will report expedited all SUSARs to the competent authority, the Medicine Evaluation Board and the competent authorities in other member states.

The expedited reporting will occur not later than 15 days after the sponsor has first knowledge of the adverse reactions. For fatal or life threatening cases the term will be maximal 7 days for a preliminary report with another 8 days for completion of the report.

#### **8.4. Annual safety report**

In addition to the expedited reporting of SUSARs, the sponsor will submit, once a year throughout the clinical trial, a safety report to the accredited METC, competent authority, Medicine Evaluation Board and competent authorities of the concerned Member States.

This safety report consists of:

- A list of all suspected (unexpected and expected) serious adverse reactions, along with an aggregated summary table of all reported serious adverse reactions, ordered by organ system
- A report concerning the safety of the subjects, consisting of a complete safety analysis and an evaluation of the balance between the efficacy and the harmfulness of the medicine under investigation.

#### **8.5. Follow-up of adverse events**

All adverse events will be followed until they have abated, or until a stable situation has been reached. Depending on the event, follow up may require additional tests or medical procedures as indicated, and/or referral to the general physician or a medical specialist.

#### **8.6. Data Safety Monitoring Board (DSMB)**

[name][name], neurologist / epidemiologist and [name]. [name], neurologist / neuro-immunologist at Erasmus MC, will serve as members of the independent data- and safety monitoring committee. The committee assesses the progress of the trial, the safety data and the efficacy endpoints and records whether to continue, modify or stop the trial every 6 months and will report their findings to the steering-committee (prof. dr. [name], dr. [name], prof. dr. [name] and prof. dr. [name])

## 9. STATISTICAL ANALYSIS

The analysis will be by intention-to-treat. A simple first analysis is to compare outcomes from the 44 patients who received a second IVIg course with the 44 patients who received placebo.

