### 3. STUDY DESIGN

A double-blind randomized placebo-controlled trial design will be used in selected patients with a poor prognosis. In patients with a good prognosis the study will have an observational design.

- All GBS patients in need of IVIg treatment, according to the treating neurologist, in a standard dosage of 2 g/kg in 2-5 consecutive days are potentially eligible for this study after obtaining informed consent.
- When patients sign 'Informed consent' they principally agree to be randomized to get a second IVIg dose or placebo when having a poor prognosis at day 7 and to be followed up for 6 months.
- Patients with the poorest prognosis based upon the modified EGOS (mEGOS 6-12) after the first IVIg course will be randomized to get a second course of IVIg (Nanogam®) in a dosage of 8 ml/kg (=0,4 g/kg) for 5 days or placebo (GPO®) in a dosage of 8 ml/kg for 5 days in a blinded fashion.
- mEGOS must preferentially be assessed 7 days after start of first IVIg course, with a range to 8 or 9 days. Trial medication needs then to be started within 24 hours when indicated according to the mEGOS score (see figure 4).
- Patient follow-up will be 6 months.
- Total patient inclusion will end when 44 patients with a poor prognosis received a second IVIg dosage.
- After covariate adjustment, to deal with variation between patients in baseline risk and to increase statistical power, data of the placebo group and the intervention group will be compared.

This is shown in the flowchart (table 2).

[figure not shown]

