### **4.4. Sample size calculation**

- We will select patients with poorest prognosis (mEGOS 6-12), this corresponds with approximately 50% of the population.
- Calculations showed that the prognosis of this group (mEGOS 6-12) is poor both at 4 weeks (85% unable to walk unaided) and at 26 weeks (35% unable to walk unaided).
- We presume that a second dose of IVIg in patients with poor prognosis (mEGOS 6-12) will raise the percentage of patients improving on the GBS disability score at 4 weeks with 15-25%. For power analysis for our primary outcome we used an improvement of 20%.
- Assuming a 20% improvement in unadjusted data and with a dichotomous outcome (being able to walk unaided versus being unable to walk unaided) we will need ( $\alpha=0.05$  and power=0.80) 290 patients in total (145 poor and 145 good prognosis).
- The power increase through covariate adjustment and the use of the ordinal outcome may be expected to result in a reduction in required sample size of 40 to 50% [31]. This leads to a required sample size of 60% of 290 patients = 174 patients.
- Based on previous calculations 50% of 174 patients (n=87) will have a poor prognosis. This group of 87 patients will be randomized to receive a second course of IVIg (n=44) or placebo (n=44).
- We expect that a sample size of 174 patients is well feasible with approximately 3 years of accrual.

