Blinding will not be broken in case of a TRF, a TRF is defined as (1) improvement in the GBS disability score of at least one grade or improvement in the MRC sum score (0-60) of more than 5 points after completion of the first IVIg course, followed by a worsening in the GBS disability score of at least one grade or a decrease in the MRC sumscore of more than 5 points within the first months after onset of disease or (2) stabilization of the clinical course for more than 1 week after completion of the first IVIg course, followed by a worsening of at least one grade of the GBS disability score or more than 5 points on the MRC sumscore. When a TRF occurs during the trial medication course, the trial medication will be stopped and an open IVIg course will be started, as this is standard treatment for a TRF. This decision should always be taken after consultation with the trial coordination.

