### Covariate adjustment

We will use covariate adjustment, which is an established approach to deal with variation between patients in baseline risk and to increase statistical power in clinical phase III trials. (Roozenbeek et al. Critical Care Medicine, in press). Using covariate adjustment we can also compare outcomes from the 44 patients who receive a second IVIg course with the other included patients (n=130) with good and poor prognosis.

Unadjusted analysis can be expressed by the following formula, in which  $\alpha$  indicates the intercept and  $\beta$  represents the regression coefficient for the treatment:

$$\text{Log odds (favorable)} = \alpha + \beta * \text{treatment}$$

The covariate-adjusted model uses modified EGOS after first IVIg treatment as well as the treatment variable:

$$\text{Log odds (favorable)} = \alpha + \beta * \text{treatment} + \beta_1 * mEGOS$$

The increase in statistical power of covariate adjustment depends on the predictive strength of the baseline characteristics; this is difficult to quantify a priori, but the modified EGOS has a very good predictive power (AUC=0.874).

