### **11.4. End of study report**

The sponsor / principal investigator will notify the accredited METC and the competent authority of the end of the study within a period of 90 days. The end of the study is defined as the last patient's last visit. Inclusion of patients will stop after 44 patients eligible for a second dosage IVIg have been included.

In case the study is ended prematurely, the sponsor will notify the accredited METC and the competent authority within 15 days, including the reasons for the premature termination.

Within one year after the end of the study, the investigator/sponsor will submit a final study report with the results of the study, including any publications/abstracts of the study, to the accredited METC and the Competent Authority.

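### Section 9 promises intention-to-treat but names the compared groups by treatment received, and section 3 ends inclusion on a count of IVIg recipients that conflicts with sections 4.4 and 11.4

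*Protocol*

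**What the plan says.** **The comparison.** Section 9 opens with the principle "The analysis will be by intention-to-treat". The next sentence describes a first analysis that will "compare outcomes from the 44 patients who received a second IVIg course with the 44 patients who received placebo". Under Covariate adjustment, the same section adds that "we can also compare outcomes from the 44 patients who receive a second IVIg course with the other included patients (n=130"); the 130 is 174 − 44.

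Section 4.4 describes the same two groups by allocation: "This group of 87 patients will be randomized to receive a second course of IVIg (n=44) or placebo (n=44").

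**The end of inclusion.** Section 3 states: "Total patient inclusion will end when 44 patients with a poor prognosis received a second IVIg dosage". Section 11.4 states: "Inclusion of patients will stop after 44 patients eligible for a second dosage IVIg have been included".

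**Where allocation and receipt can part.** Section 7.2 provides: "When a TRF occurs during the trial medication course, the trial medication will be stopped and an open IVIg course will be started". This applies in either arm, and the blind is kept. Section 7.6 puts patients with at least one dose in the safety evaluation as a minimum and says nothing about their place in the efficacy analysis.

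**The concern.** Intention-to-treat compares patients by the arm they were allocated to. A comparison of those who received one product with those who received the other is a different analysis. Section 9 states the first and describes the second.

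The two differ for two kinds of patient. One is randomised but never starts trial medication and so has received neither product. The other is allocated to placebo, has a TRF during the trial course and is switched to open IVIg; that patient has received both placebo and a second course of IVIg, so the receipt wording does not place the patient uniquely. Both events follow randomisation and can be related to prognosis. Sorting or omitting patients on such events gives up the protection of randomisation for the week-4 result.

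The end of inclusion is a separate matter with the same root. A rule that counts IVIg recipients fixes neither the number randomised nor the size of the placebo arm, and whoever applies it must know the allocation. Section 7.2 blinds the coordinating investigator, co-investigator, site investigator, the manufacturer's trial coordinator and the patient.

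**Working it through.** **1. The planned number.** Inputs from section 4.4: 85% unable to walk unaided at 4 weeks, hence 15% able; a 20-point improvement, hence 35%; α = 0.05 (taken as two-sided, which reproduces the figure); power 0.80.

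n per arm = [1.96·√(2·0.25·0.75) + 0.842·√(0.15·0.85 + 0.35·0.65)]² / 0.20² = 72.4

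That is 144.8 randomised and, with half of all patients having a poor prognosis, 289.6 in total; the protocol gives 145 and 290. Then 0.60 × 290 = 174, half of which is 87, or 44 per arm after rounding up. So the 44 and 44 in section 9 are the allocation numbers of section 4.4.

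**2. What a literal by-receipt grouping could do with no true effect.** Let f be the share of placebo patients given open IVIg during the trial course and counted as IVIg, and q the share of those who walk unaided at week 4. Both are assumed. The protocol's only TRF figure is about 10% of GBS patients after a single course (section 1), not the rate during a five-day course begun around day 7 to 10. So f runs from 0 to 10%, with 10% as an upper case; q runs from 0 to 30%. Both arms have 44 patients and 15% walking (6.6 patients).

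Apparent difference = (6.6 + 44fq)/(44(1+f)) − (6.6 − 44fq)/(44(1−f))

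| f | q | counted as IVIg | left as placebo | difference (points) |
|---|---|---|---|---|
| 5% | 0 | 6.60/46.2 = 14.3% | 6.60/41.8 = 15.8% | −1.5 |
| 5% | 30% | 7.26/46.2 = 15.7% | 5.94/41.8 = 14.2% | +1.5 |
| 10% | 0 | 6.60/48.4 = 13.6% | 6.60/39.6 = 16.7% | −3.0 |
| 10% | 15% | 7.26/48.4 = 15.0% | 5.94/39.6 = 15.0% | 0 |
| 10% | 30% | 7.92/48.4 = 16.4% | 5.28/39.6 = 13.3% | +3.0 |

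Standard error of the difference at 15% in both arms: √(2·0.15·0.85/44) = 7.6 points. The largest shift is 3.0/7.6 = 0.4 standard errors.

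**3. What the section 3 rule does to the randomised total.** Let d be the share in each arm who never start (assumed 0 to 10%) and N the number randomised per arm. Counting open IVIg in placebo patients as receipt, inclusion ends in expectation when N(1−d)(1+f) = 44.

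- d = 0, f = 0: N = 44.0, total 88.
- d = 0, f = 10%: N = 44/1.10 = 40.0, total 80.
- d = 10%, f = 0: N = 44/0.90 = 48.9, total 98.
- d = 10%, f = 10%: N = 44/0.99 = 44.4, total 89.

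If open courses are not counted, the range is 88 to 98.

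**4. The statements on numbers side by side.** Section 4.4: 87 randomised, 44 per arm. Section 3: stop at 44 IVIg recipients, which means about 80 to 98 randomised. Section 11.4: stop at 44 patients eligible for the second course. Eligibility is settled before randomisation, so read literally this is 44/87, about half of the planned number. The three do not agree.

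**The case against.** The strongest reply is that the governing principle is explicit. Section 9 begins with intention-to-treat, the sentence after it only introduces a simple first analysis, and its 44 and 44 are the allocation numbers of section 4.4. A true by-receipt analysis could not know in advance that 44 patients would receive placebo. All of this stands, and it makes loose wording the likelier explanation.

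A reader might go further in four ways that the protocol does not support.

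- *That patients will change group or be dropped.* No section reassigns anyone by treatment received or excludes anyone from the efficacy analysis. A placebo patient switched for a TRF under section 7.2 has already started placebo, and that section names the open course separately from the blinded one. Misplacement is possible under the wording; it is not the stated plan.
- *That section 3 makes the 44 analysed the recipients by construction.* A rule for ending inclusion says when recruitment stops, not who is analysed. It moves and removes nobody.
- *That recruiting to a count of recipients contradicts section 7.5.* That section concerns replacement after withdrawal. A non-starter who stays in the analysis has not been replaced.
- *That 10% of placebo patients would cross over.* The 10% is not tied to the trial course, and the rate in that window is unknown.

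It can also be said that analysis sets are commonly detailed in a statistical analysis plan, which is not at hand. A missing definition would therefore be no finding. What remains is that the protocol describes one comparison in two incompatible ways. On blinding, a pharmacy or the safety board could keep the count of recipients, but the protocol gives that task to nobody.

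**Conclusion.** The point holds as a conflict between stated rules, not as evidence that the trial will be analysed by treatment received. Intention-to-treat is probably intended; the wording in section 9 would still let someone group by receipt and claim to follow the protocol.

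The possible effect on the result is modest: no more than about 3 points either way under no effect, roughly 0.4 standard errors, and zero if the affected patients walk at the average rate. That bound rests on the assumed 0-10% crossover and 0-30% walking.

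The inconsistency over the end of inclusion is firmer, because it needs no reading of intent: sections 3, 4.4 and 11.4 lead to different numbers randomised. The 80 to 98 range rests on the assumed shares; the conflict between the three sections does not. Both matters should be corrected.

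**What to change.** 1. In the opening of section 9, define the comparison as *all patients randomised to a second IVIg course against all patients randomised to placebo, regardless of trial medication or open IVIg received*. Under Covariate adjustment, define the IVIg group, and the placebo patients among the other 130, by allocation in the same way.
2. If a comparison by treatment received is wanted, label it a sensitivity analysis.
3. Give one end-of-inclusion rule in sections 3 and 11.4, as the total number randomised in section 4.4, and settle whether that is 87 or 88 (44 per arm). A total randomised can be counted without opening the allocation.

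The cost is a change of wording in four places. It needs no new data and leaves the planned sample size as it is. No change to the treatment of a TRF is proposed.

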### Covariate adjustment

We will use covariate adjustment, which is an established approach to deal with variation between patients in baseline risk and to increase statistical power in clinical phase III trials. (Roozenbeek et al. Critical Care Medicine, in press). Using covariate adjustment we can also compare outcomes from the 44 patients who receive a second IVIg course with the other included patients (n=130) with good and poor prognosis.

Unadjusted analysis can be expressed by the following formula, in which  $\alpha$  indicates the intercept and  $\beta$  represents the regression coefficient for the treatment:

$$\text{Log odds (favorable)} = \alpha + \beta * \text{treatment}$$

The covariate-adjusted model uses modified EGOS after first IVIg treatment as well as the treatment variable:

$$\text{Log odds (favorable)} = \alpha + \beta * \text{treatment} + \beta_1 * mEGOS$$

The increase in statistical power of covariate adjustment depends on the predictive strength of the baseline characteristics; this is difficult to quantify a priori, but the modified EGOS has a very good predictive power (AUC=0.874).

### Proportional Odds model

Furthermore, we can consider the full GBS disability score at 4 weeks as an ordinal outcome, rather than dichotomize as  $\leq 2$  vs  $>2$ . Analysis will then be with a proportional odds regression model. The proportional odds model provides a more sensitive analysis than would be possible by arbitrarily dichotomizing the outcome variable and does so without imposing unverifiable assumptions regarding the structure of the data[32]. The disadvantage is that we have to make the assumption of proportional odds, i.e. that the treatment effect (as an odds ratio) is identical across all possible cut-offs for the GBS disability score. This assumption will be assessed by a test for heterogeneity of effect across cut-offs.

Further exploratory analyses will be performed using appropriate statistical summary measures (medians, means, standard deviations, standard errors, interquartile ranges) and statistical tests (both parametric and non-parametric).

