## 7. METHODS

### 7.1. Study parameters/endpoints

#### 7.1.1. Main study endpoint

GBS disability score at 4 weeks after start of first IVIg course. The full range of scores will be considered as an ordinal outcome scale. In analyzing we will use a proportional odds model. (Extent of) improvement on this ordinal scale will be compared between groups.

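### Section 7.1.1 commits to a proportional odds model, but section 9 writes binary models and leaves the ordinal scale optional, although the cut to 87 randomised patients relies on an adjusted ordinal analysis

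*Protocol*

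**What the plan says.** Section 7.1.1 takes the full range of the GBS disability score at 4 weeks as an ordinal outcome and is definite about the model: "In analyzing we will use a proportional odds model". It does not mention adjustment.

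Section 9 runs in this order:

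- Analysis is by intention to treat, and "A simple first analysis is to compare outcomes from the 44 patients who received a second IVIg course with the 44 patients who received placebo". No outcome scale is named.
- Under Covariate adjustment, the protocol commits to adjusting. It writes an unadjusted and an mEGOS-adjusted model, each for the log odds of a favorable outcome with one intercept, which is a binary logistic form. It adds that the 44 treated patients can also be compared with the other 130 included patients.
- Under Proportional Odds model, introduced as a further step, it says that "we can consider the full GBS disability score at 4 weeks as an ordinal outcome, rather than dichotomize" at 2 or below versus above 2. If so, a proportional odds regression follows, which the text describes as more sensitive.

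Section 4.4 sizes the trial first for an unadjusted dichotomous outcome: 290 patients, of whom 145 have a poor prognosis and are randomised. It then argues: "The power increase through covariate adjustment and the use of the ordinal outcome may be expected to result in a reduction in required sample size". The saving is put at between 40% and 50%. Using 40%, it arrives at 174 patients, of whom 87 are randomised.

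**The concern.** The endpoint section commits to the ordinal model, while the analysis section treats it as an option after writing out binary models. Neither section labels one analysis as the test of the primary objective, and 7.1.1 does not say whether mEGOS is in the model. An analyst who implements the section 9 formulas as written would run a dichotomous test on a sample that was reduced because the analysis would not be dichotomous.

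Two things are at stake. The first is power: the 40% reduction is justified only for the combination of ordinal scale and adjustment. The second is the error rate: with several candidate analyses and none ranked, the text leaves room to choose after seeing results.

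**Working it through.** **Inputs, all from section 4.4.** Control: 85% unable to walk unaided at 4 weeks, so 15% able. Effect: 20 percentage points, so 35% able. Alpha 0.05, power 0.80. Sidedness is not stated; two-sided is inferred because it reproduces the protocol's figure. Reduction 40%.

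**Step 1. Reproduce the protocol's figure.** Two proportions, pooled variance, no continuity correction, mean proportion 0.25:

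n per arm = [1.960·√(2·0.25·0.75) + 0.842·√(0.15·0.85 + 0.35·0.65)]² / 0.20²
= [1.200 + 0.501]² / 0.04 = 72.4

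Two arms: 144.8, i.e. 145. Doubled for the half with good prognosis: 290. Then 0.6 × 290 = 174, and half of that is 87. One-sided testing gives 114 and a continuity correction gives 166, so neither fits 145.

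**Step 2. Unadjusted dichotomous power at the reduced size.** Power = Φ[(0.20·√n − 1.200)/0.596].

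- n = 43.5 per arm (87 patients): Φ[(1.319 − 1.200)/0.596] = Φ(0.199) = 57.9%
- n = 44 per arm: Φ[(1.327 − 1.200)/0.596] = Φ(0.212) = 58.4%
- Fisher's exact test, 44 per arm: 48.8%

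At the ends of the protocol's own 15 to 25 point range, power with 87 patients is 38.6% and 75.1%.

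**Step 3. Adjusted dichotomous power.** If adjustment alone saves a fraction r of the sample, the effective size per arm is 43.5/(1 − r).

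| r | effective n per arm | power |
|---|---|---|
| 10% | 48.3 | 62.5% |
| 20% | 54.4 | 67.8% |
| 30% | 62.1 | 73.6% |
| 40% | 72.5 | 80.1% |

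The 80% returns only if adjustment delivers the entire 40%. Section 4.4 credits that figure to adjustment and the ordinal scale together, and section 9 concedes that the gain from adjustment is hard to put a figure on in advance.

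**Step 4. Ordinal power (assumptions needed).** The protocol gives no distribution over the score. The common odds ratio implied by 15% versus 35% is (0.35/0.65)/(0.15/0.85) = 3.05. Whitehead's formula gives N = 12·(1.960 + 0.842)² / [(ln 3.05)²·(1 − Σp̄³)] = 75.7/(1 − Σp̄³), where p̄ is the mean proportion of the two arms in each category. Four assumed control distributions, each with 15% at scores 0 to 2:

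| control, scores 0 to 6 (%) | N for 80% | power with 87 |
|---|---|---|
| 0, 5, 10, 20, 40, 22, 3 | 80.6 | 82.9% |
| 0, 2, 13, 10, 50, 22, 3 | 84.6 | 81.1% |
| 1, 4, 10, 30, 30, 22, 3 | 80.4 | 83.0% |
| 0, 1, 14, 5, 65, 12, 3 | 95.7 | 76.1% |

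With only two categories the same formula gives 61.5%. That is the like-for-like comparator and is slightly more favourable than the 57.9% of step 2.

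For the effect of mEGOS adjustment, simulation at 44 per arm used mEGOS uniform on 6 to 12, one assumed score distribution and 400 runs per setting. At log-odds slopes of 0.2, 0.5 and 0.8 per point, power was 82%, 91% and 98% for the adjusted ordinal model, and 59%, 69% and 79% for the adjusted dichotomous model. Two larger simulations at slope 0.5 (3,000 and 5,000 runs, with approximations in the larger) gave 91% and 88% ordinal, and 62% and 65% dichotomous.

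**Step 5. Choosing among the analyses.** Under no effect, with assumed distributions, at least one of the four within-trial analyses (dichotomous or ordinal, unadjusted or adjusted) had p < 0.05 in 11.7% of 3,000 runs and 11.9% of 5,000 runs. Adding the comparison with 130 patients gave 12.6% in the 3,000-run simulation.

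**The case against.** Read together, the protocol already points to the right analysis. Section 7.1.1 is definite on scale and model, section 9 is definite on adjustment and names mEGOS, section 3 says the arms are compared after covariate adjustment, and section 9 fixes intention to treat. Section 9 can be read as an exposition that builds from a simple comparison to adjustment to the ordinal model, which it argues for. This largely stands: the intended analysis can be inferred. It does not remove the conflict, because the analysis section makes the model conditional, writes the adjusted model in binary form, and never combines adjustment and ordinal scale in one named primary test. Nor is this detail that may wait for the SAP: the protocol takes two positions, and an SAP could follow either.

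Several stronger readings are tempting but not supported:

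- *Section 9 makes a dichotomous comparison primary or puts one first.* The opening comparison names no scale, and nothing calls a dichotomous analysis primary. The binary reading comes from the formulas and the later remark on dichotomizing.
- *Nothing fixes the analysis.* Section 7.1.1 does name the model.
- *The 80% holds only for the ordinal scale.* Section 4.4 credits scale and adjustment jointly, and with a steep assumed mEGOS slope the adjusted dichotomous test comes close (79%).
- *The type I error is 12%.* That applies only if the best result is picked. No such selection is planned; section 9 merely does not rule it out.

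**Conclusion.** The point holds as a conflict between 7.1.1 and section 9 that bears on the basis for the sample size. The firm figure is about 58% power against the stated 80% for an unadjusted dichotomous test with 87 to 88 patients. It uses only the protocol's inputs, with two-sidedness inferred from reproducing 145. The 63 to 74% for an adjusted dichotomous test follows from assumed savings of 10 to 30%.

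The ordinal powers and the roughly 12% error rate are illustrations: they depend on score distributions and mEGOS slopes that the protocol does not give. A reader might infer that the trial is underpowered as designed. The figures do not show that: under the assumptions tried, the adjusted ordinal analysis reaches 80%. The shortfall arises only if the binary formulas of section 9 are followed for the primary test.

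**What to change.** State the same sentence in 7.1.1 and section 9: the single primary analysis is a proportional odds model for the full GBS disability score at 4 weeks, with treatment and mEGOS as covariates, in all randomised patients by assigned arm, tested two-sided at 0.05. Rewrite the adjusted formula in section 9 in its ordinal form, and replace the permissive wording with a commitment. Label the unadjusted comparison, the dichotomous models and the comparison of 44 with 130 patients as supportive, so that none can replace the primary result. Make the change before unblinding.

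What to do if the proportionality test fails can be left to the SAP.

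The cost is wording only. The one loss is that the simpler analyses, which are easier to explain, give up any claim to primary status.
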